## 7.5 Stopping Rules

The Principal Investigator may terminate the trial after consultation with the appropriate consulting staff at any time.

Patients with grade 3 or 4 toxicity during the infusion will have their cellular administration discontinued immediately and the event noted as a dose limiting toxicity.

The study as a whole will be halted if 2/5 patients develop grade 3-4 infusion reactions, or grade 4 organ toxicity within the first 30 days following Treg infusion. The study will also be halted if a death results from any of the criteria listed above.

If two of three consecutive subjects receiving experience severe steroid resistant acute rejection, vascular acute rejection, graft loss, malignancy, severe infection, and/or death in a period of 3 months, enrollment will be stopped and the study reassessed by the investigators, the IND sponsor and IND medical monitor.

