### TREATMENT SCHEMA

EXPERIMENTAL: TRACT (N=12)  
AUTOLOGOUS TREG INFUSION

Kidney transplantation using standard of care immunosuppressive agents will be performed, followed by intravenous infusion of autologous, expanded Tregs (TRACT) at day 60 after transplantation. Subjects will be administered only one dose of Treg at the specified dose level. Cell infusions will be escalated in the absence of adverse events within 30 days of infusion using the following schema:

Tier 1:  $0.5 \times 10^9$  total expanded nTregs (n=3)

Tier 2:  $1 \times 10^9$  total expanded nTregs (n=3)

Tier 3:  $5 \times 10^9$  total expanded nTregs (n=3)

Tier 4:  $8 \times 10^9$  total expanded nTregs (n=3)

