| $\geq 2$                                       | Dose escalation will be stopped. This dose level will be declared the maximally administered dose (highest dose administered). Three additional patients will be entered at the next lowest dose level if only 3 patients were treated previously at that dose level. |
| 1 out of 3                                     | Enter at least 3 more patients at this dose level. 
 
If 0 of these 3 patients experience DLT, proceed to the next dose level.
 
                                                                                         |

|                                                                          |                                                                                                                                                                                                                                                                                                                      |
|--------------------------------------------------------------------------|----------------------------------------------------------------------------------------------------------------------------------------------------------------------------------------------------------------------------------------------------------------------------------------------------------------------|
|                                                                          | 
 
If 1 or more of this group suffer DLT, then dose escalation is stopped and this dose is declared the maximally administered dose. Three additional patients will be entered at the next lowest dose level if only 3 patients were treated previously at that dose.
 
 |
| ≤ 1 out of 6 at highest dose level below the maximally administered dose | This will be the Maximum Tolerated Dose (MTD). At least 6 patients will be entered at this dose.                                                                                                                                                                                                                     |

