Once a cohort is filled, enrollment into the next dose level will only begin after all patients in that cohort have passed through the DLT observation period. At that point, the PI, IND Sponsor, IND Medical Monitor and study co-investigators will review toxicity reports and recommend whether or not it is safe to proceed to the next cohort.

After escalation has stopped, de-escalation will begin at one dose level below the maximum achieved during escalation. The action taken depends on the number of patients previously treated at a dose level. If 3 or fewer patients have previously been treated, 3 patients are added; if 6 patients have previously been treated, this level will be declared to be the MTD. The MTD is defined to be the highest dose level at which no more than 1 of 6 treated patients experiences a DLT.

Patients within a cohort need not be accrued or treated at the same time; thus, accrual at a dose level should stop as soon as 2 patients at a dose level have experienced DLT at that level. There will be no intra-patient dose escalation or de-escalation.

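### The 2/5 halting rule in Section 7.5 does not say which five patients it counts, and nothing says whether it or Section 7.4 governs when both are triggered

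*Protocol*

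**What the plan says.** The Treatment Schema plans 12 patients in four tiers of three. Section 7.4 allows a cohort to grow to six.

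**Section 7.5 (study level).** "The study as a whole will be halted if 2/5 patients develop grade 3-4 infusion reactions", with a second limb for "grade 4 organ toxicity within the first 30 days following Treg infusion". I read the 2/5 count as covering both limbs, though the sentence does not settle that. The section's last rule does define its window: "If two of three consecutive subjects receiving experience severe steroid resistant acute rejection".

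**Section 7.4 (dose level).** After two or more DLTs at a level, escalation stops and "Three additional patients will be entered at the next lowest dose level if only 3 patients were treated previously at that dose level". The section also says that "accrual at a dose level should stop as soon as 2 patients at a dose level have experienced DLT at that level".

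**The link between them.** Both sections say that a patient with grade 3 or 4 toxicity during the infusion has "cellular administration discontinued immediately and the event noted as a dose limiting toxicity" (wording from 7.5; 7.4 differs only trivially). The DLT definition in 7.4, however, excludes infusion reactions that respond to supportive care, and it covers the first 3 weeks after dosing, against 30 days in 7.5.

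**The concern.** A halting rule is applied in real time by the people running the trial, so it has to give one answer for one set of data. This one does not, for three reasons.

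- **Undefined denominator.** Two of five could mean the first five treated, any five consecutive patients, or a running rate of 40%. The cohort structure does not help, because five is neither three nor six.
- **Possible lapse.** If the first five are meant, the rule has been used up by the second patient of Tier 2. It cannot respond to events at the two highest cell doses.
- **Two instructions for one event pattern.** Two grade 3-4 infusion toxicities in one cohort above Tier 1 can lead one reader to halt the study and another to treat three more patients at the level below.

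At stake is whether further patients are infused after a safety signal, in a trial whose primary objective is safety.

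**Working it through.** The protocol gives no halting probability and no expected event rate, so there is no stated figure to reproduce. The event rate p per patient is my assumption, shown from 5% to 30%. The base case has 12 patients in sequence, a constant p, independent outcomes and no cohort expansion.

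**1. Which patients does each reading cover?** With cohorts of three, Tier 1 is patients 1-3, Tier 2 is 4-6, Tier 3 is 7-9 and Tier 4 is 10-12. The first five are therefore all of Tier 1 and two patients of Tier 2. If Tier 1 is expanded to six, they are all in Tier 1. Either way, nobody in Tiers 3 or 4 is counted.

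**2. Chance of a halt.** Write q = 1 - p.

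- First five: 1 - q^5 - 5pq^4. At 10%: 1 - 0.5905 - 0.3281 = 0.081.
- Any five consecutive: there is no halt only if all events lie at least five positions apart. The numbers of such arrangements of 0, 1, 2 and 3 events among 12 patients are 1, 12, 28 and 4. The chance of a halt is 1 - (q^12 + 12pq^11 + 28p²q^10 + 4p³q^9). At 10%: 1 - (0.2824 + 0.3766 + 0.0976 + 0.0015) = 0.242.
- Running rate of at least 40% from the fifth patient: enumeration of all 2^12 = 4,096 outcome sequences.

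| Assumed p | First five | Running 40% | Any five consecutive | Any five ÷ first five |
|---|---|---|---|---|
| 5% | 2.3% | 2.3% | 7.6% | 3.4 |
| 10% | 8.1% | 8.7% | 24.2% | 3.0 |
| 20% | 26.3% | 30.1% | 60.1% | 2.3 |
| 30% | 47.2% | 55.8% | 83.9% | 1.8 |

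**3. Sensitivity.** Following the Section 7.4 path with its expansions (200,000 simulated trials) gives 8.1% v 31.7% at p = 10% for first-five against any-five-consecutive. With assumed rates rising by tier (5, 10, 20, 30%) and 12 patients, the figures are 4.2% v 52.0%.

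**4. When do 7.4 and 7.5 clash?** Three conditions are needed:

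- Two events that count under both sections fall in one cohort.
- That cohort is above Tier 1, since Tier 1 has no lower level, and only three patients were treated at the level below.
- Both events are among the counted five.

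The chance of two or more events in a cohort of three is P = 3p²q + p³, which is 0.028, 0.104 and 0.216 at 10%, 20% and 30%. The chance of at least one such cohort in Tiers 2-4 is 1 - (1 - P)^3:

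- 10%: 1 - 0.972³ = 8%
- 20%: 1 - 0.896³ = 28%
- 30%: 1 - 0.784³ = 52%

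Under any-five-consecutive, every such cohort also meets 2/5. Under first-five, only patients 4 and 5 can produce the clash, with chance p²: 1%, 4% and 9%.

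**5. Do both sections count the same events?** Not always. A grade 3-4 infusion reaction that responds to supportive care counts toward 2/5 in 7.5. In 7.4 it is excluded by the DLT definition, yet it is a DLT under the during-infusion sentence in both sections. A grade 4 organ toxicity on days 22-30 counts in 7.5 but falls outside the 3-week DLT window.

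**The case against.** The best reply is that halting the study as a whole is study-level language and 7.4 works at dose level, so a halt would naturally override. That is a sensible reading, but the protocol does not state it, nor what follows a halt. The neighbouring rule, by contrast, says that enrollment stops and the study is reassessed.

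A second reply is that the assumed rates may be too high. The nearest figure in the protocol is the infusional toxicity table in Section 1.4, with one grade 3 entry among 23 patients (4.3%). At 1/23 the three readings give 1.7% (first five), 1.8% (running 40%) and 5.9% (any five consecutive). This stands: the absolute chances may be small, and two of the readings nearly coincide at low rates. It does not settle which rule applies once two events have occurred.

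Three stronger readings are tempting and are not supported:

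- **That Tiers 3 and 4 could be left without protection.** They would not be. The halt for a qualifying death, the two-of-three-consecutive rule, the accrual stop at two DLTs, the 21-day follow-up before the next patient and the review before each cohort all remain, and the principal investigator may terminate the trial at any time. Only the 2/5 rule would lapse.
- **That the de-escalation in 7.4 could never operate for these toxicities.** It could. In a cohort expanded to six, events in the first and sixth patients stop escalation under 7.4, yet no five consecutive patients within that cohort contain both. Under first-five, any two events after patient 5 also leave 7.4 free to run.
- **That three-fold is the limit of the discrepancy.** It is the ratio at an assumed 10% rate. It falls to 1.8 at 30% and rises to 3.4 at 5%, and it is far larger if toxicity rises with dose.

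The absence of a table of halting probabilities is no finding, since that may sit in the analysis plan.

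**Conclusion.** The point holds. The five patients are undefined, one plausible reading makes the 2/5 rule inactive in Tiers 3 and 4, and Sections 7.4 and 7.5 can prescribe incompatible actions for the same two events with no stated precedence. The DLT exclusion for infusion reactions and the 3-week against 30-day windows add to the conflict. These are textual findings and need no assumed event rate.

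The size does rest on assumptions: independent patients, a constant rate, 12 treated and no expansion. On that basis the choice of reading moves the chance of a halt from 8% to 24% at a 10% rate and from 47% to 84% at 30%. The pattern that sets the sections against each other arises in about 8%, 28% and 52% of trials at rates of 10%, 20% and 30% if any five consecutive patients count, and far less often if only the first five do. The sponsor should correct this.

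**What to change.** - In 7.5, replace 2/5 patients with an explicit count and window: which patients are counted, from which patient onward, whether the rule stays active through all four tiers and any expansion, and whether the count applies to both limbs.
- State which section governs when the same events trigger both, and what follows a halt. Cross-refer from 7.4.
- Reconcile the DLT status of grade 3-4 infusion reactions across the opening of 7.4, its DLT definition and 7.5, and reconcile the 21-day and 30-day windows.
- Optionally, tabulate the chance of halting under the chosen wording at a few assumed rates.

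The threshold, the windows and the governing rule are for the sponsor to decide. The cost is a few sentences in an amendment, with no extra patients or procedures.

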## SCHEDULE OF EVENTS: SAMPLE COLLECTION FOR TRACT STUDY

[figure not shown]

Escalating doses of autologous expanded Tregs (TRACT) will be administered to the next cohort of patients if there are no observed serious adverse events within 30 days of TRACT infusion as follows:

Tier 1:  $0.5 \times 10^9$  total expanded Tregs (n=3)

Tier 2:  $1 \times 10^9$  total expanded Tregs (n=3)

Tier 3:  $5 \times 10^9$  total expanded Tregs (n=3)

Tier 4:  $8 \times 10^9$  total expanded Tregs (n=3)

Patients will be monitored at various time points, as described above for evidence of donor-specific transplantation tolerance using in vitro analyses, specifically mixed-leucocyte reaction assays (MLR). Graft function will be monitored clinically in the standard fashion. The overall goal for this phase I study is to demonstrate the safety of TRACT administration in kidney transplant recipients, and lay the foundation for a subsequent phase 2 trial. If we are successful, this approach could have for a transformative effect upon the field of solid organ and cellular transplantation.

The clinical site for recruitment, enrollment, and treatment of patients will be Northwestern Memorial Hospital. The Principal Investigator is part of a team with the most active living donor renal transplant program in the nation, with more than 160 such transplants performed in 2011. There already exists a robust infrastructure for combined therapeutic cell transfer (stem cell) and solid organ transplantation with two protocols for living donor renal transplants + HSC having been active at Northwestern for almost 5 years; [name], the IND sponsor and co-investigator, serves as PI or co-PI on these trials (50, 51).

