## 4.2 Primary Safety Endpoint

The primary safety endpoint is the evaluation of cellular related toxicities immediately and within 24 hours post-infusion of TRACT. Since TRACT is being administered to promote immunosuppression and prevent rejection, specific adverse events (subsequent rejection episodes, allosensitization, development of opportunistic infection) within 30 days of infusion will be monitored.

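### Section 7.5 sets no mandatory response to a single death outside infusion reaction or organ toxicity, its two-of-three rule does not accumulate, and 4.1 and 7.4 disagree on the same event

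*Protocol*

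**What the plan says.** Section 7.5 contains four provisions that matter here.

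- A discretionary stop: "The Principal Investigator may terminate the trial after consultation with the appropriate consulting staff at any time".
- A study halt: "The study as a whole will be halted if 2/5 patients develop grade 3-4 infusion reactions, or grade 4 organ toxicity", counted over the first 30 days after infusion.
- Directly after it, the single-death halt: "The study will also be halted if a death results from any of the criteria listed above".
- In the next paragraph, a composite rule: "If two of three consecutive subjects receiving experience severe steroid resistant acute rejection, vascular acute rejection, graft loss, malignancy, severe infection, and/or death", within 3 months. Its consequence is that "enrollment will be stopped and the study reassessed by the investigators" together with the IND sponsor and IND medical monitor.

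Two other sections govern escalation. Section 4.1 makes it depend on the absence, within 30 days, of infusion-related effects, rejection, allosensitization and opportunistic infection. Under the schedule of events that follows, the next cohort is dosed "if there are no observed serious adverse events within 30 days of TRACT infusion". Section 9.1 classes any fatal adverse event as serious. Section 7.4 allows escalation once the patients at a level have been followed for at least 21 days without a dose-limiting toxicity (DLT).

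Section 4.2 explains the interest in infection: "Since TRACT is being administered to promote immunosuppression and prevent rejection, specific adverse events" (rejection, allosensitization, opportunistic infection) are to be monitored for 30 days.

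**The concern.** The single-death halt refers back to criteria that do not include infection, malignancy or graft loss. Those appear only in the paragraph after it, where one death is one item in a composite that needs two affected subjects. The protocol watches opportunistic infection because the product is meant to promote immunosuppression, so a death of that kind should meet a clear and consistent written response. Instead, the response depends on which section is read, on the day of the event, and on where the affected subjects fall in the infusion sequence. At stake is whether dosing pauses after a death in a small dose-escalation trial, and whether isolated deaths in successive tiers are ever counted together by rule.

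**Working it through.** **1. Scope of the single-death halt.** The items above that sentence in 7.5 are grade 3 or 4 toxicity during infusion, grade 3-4 infusion reactions, and grade 4 organ toxicity within 30 days. Infection, malignancy and graft loss are not among them. The protocol gives no error rate or stopping probability for 7.5, so there is no stated figure to reproduce.

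**2. What two-of-three can miss.** Inputs: 12 infused subjects (Study Summary; four tiers of three), taken in infusion order. The rule fires if any three consecutive subjects include at least two with a listed event. It is silent only if successive affected subjects are at least three positions apart. For k affected subjects among N = 12:

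silent orderings = C(N − 2(k − 1), k), out of C(N, k)

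| Affected subjects | Silent orderings | All orderings | Share silent |
|---|---|---|---|
| 1 | C(12,1) = 12 | 12 | 100% |
| 2 | C(10,2) = 45 | 66 | 68% |
| 3 | C(8,3) = 56 | 220 | 25% |
| 4 | C(6,4) = 15 | 495 | 3% |
| 5 or more | 0 | – | 0% |

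The 3-month condition can only add silent cases. The shares describe this rule in isolation and need no event rate.

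**3. Illustration with assumed rates.** The protocol gives no per-subject probability p for a listed event, so 5%, 10% and 20% are assumed. After one infection death, the rule needs a listed event in one of at most four neighbours (two before, two after):

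P(second event) = 1 − (1 − p)^4

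- p = 5%: 1 − 0.95^4 = 19%
- p = 10%: 1 − 0.90^4 = 34%
- p = 20%: 1 − 0.80^4 = 59%

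These assume independent subjects. They are upper values for the stated p, because the 3-month limit is ignored and subjects at either end of the sequence have fewer neighbours.

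**4. One fatal infection, three sections.**

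| Timing after infusion | 4.1 | 7.4 | 7.5 |
|---|---|---|---|
| Up to day 21 | Bars escalation | A DLT only under conditions (below) | Two-of-three only |
| Days 22-30 | Bars escalation | Outside the DLT window; 0 of 3 leads to the next level, subject to review | Two-of-three only |
| After day 30 | No provision | No provision | Two-of-three only |

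The 7.4 conditions are narrow. The definition names grade 3 or 4 and not death, exempts infections related to neutropenia, and excludes events attributed to the transplant, intercurrent illness or concomitant medication. Sections 2.1 and 6.1 give every subject alemtuzumab and mycophenolate, and 2.1 lists neutropenia as an adverse event of both. A fatal infection inside 21 days could therefore also fail to count as a DLT. If it did count, one DLT in three expands the cohort and does not stop the study.

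**The case against.** The strongest reply is that the protocol responds to such a death in several ways outside 7.5. Section 4.1 bars escalation after any serious adverse event or opportunistic infection within 30 days. Section 7.4 requires a safety review before the next patient at a level and before the next cohort. Section 8.1 has weekly toxicity review and discusses closing accrual. Section 9.4 has the number and type of serious adverse events assessed regularly, with review before each escalation. The investigator may terminate at any time. Judgement rather than an automatic halt is a defensible choice for one death of uncertain cause.

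Much of this stands, and it rules out several stronger readings.

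- A reader might infer that one infection death halts nothing and that escalation simply continues. Section 4.1 contradicts that for the first 30 days.
- A reader might take the second event to be needed in the next two subjects. The wording counts preceding subjects too, and any listed event qualifies.
- A reader might picture deaths in subjects 1, 4, 7 and 10, one per tier, passing unnoticed. That pattern is silent in 7.5, but it passes 4.1 only if every death falls after day 30, and the reviews would still see it.
- A reader might take 4.2 to call infection the expected harm of the product. It says only that infection will be monitored, and sections 1.2 and 1.3 report no pan-immunosuppression in preclinical work.

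The reply does not close the gap. The 4.1 bar ends at day 30 and governs escalation, not further infusions in the same tier. The reviews carry no threshold for death or infection. Section 7.4 does not match 4.1.

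**Conclusion.** The point holds in this limited form. Section 7.5 contains no mandatory response to a single death from infection, malignancy or graft loss, and its composite rule does not accumulate (silent in 68%, 25% and 3% of orderings for 2, 3 and 4 affected subjects among 12). Sections 4.1 and 7.4 can give opposite escalation answers for the same fatal infection, most plainly on days 22-30. After day 30 two-of-three is the only pre-set rule left.

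This rests on the plain reading of the back-reference in 7.5. The reference is undefined, and a septic death with organ failure within 30 days might be read as organ toxicity. The counts also assume 12 infused subjects, taken consecutively in infusion order. The documents do not support the conclusion that such a death goes unreviewed or that early escalation is unrestricted.

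**What to change.** Reconcile sections 4.1 (including the schedule of events), 7.4 and 7.5 so that they give one consistent response to a death or serious infection after TRACT, with one observation window and one set of qualifying events for escalation. In 7.5, define which criteria the single-death sentence refers to. State how a single death is handled, and how deaths accumulating over all infused subjects are handled, using the reviewers already named in 7.4, 7.5 and 9.4. The choice of rule is the sponsor's. The cost is a short protocol amendment; no new committee or data collection is needed.

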| Study Products                        | Autologous, ex vivo expanded natural regulatory T cells (Tregs)                                                                                                               |
| Duration of administration            | Single infusion of expanded Tregs day +60 following living donor kidney transplantation                                                                                       |
| Statistical Methodology               | Mann-Whitney, Fisher test, Student’s t test, Anova and Chi-Squared analyses will be used to analyze the safety data as needed.                                                |

ESTIMATED ENROLLMENT: 12

STUDY START DATE: MARCH 2014

ESTIMATED STUDY COMPLETION: MARCH 2016

ESTIMATED PRIMARY COMPLETION DATE: APRIL 2015

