### **1.9 Approach**

We propose to use our knowledge gained from small animal and preclinical human studies to embark on an investigational pathway for clinical application of ex vivo expanded human nTregs as adoptive cellular therapy (TRACT). This is both extremely innovative and potentially very significant – TRACT with recipient derived Tregs could allow for significant reduction and perhaps elimination of immunosuppressive medications in organ transplantation. Although TRACT with ex-vivo manipulated Tregs have recently been initiated in the context of stem cell transplantation for the prevention of graft versus host disease, our clinical trial represents the first use of recipient-derived Tregs in an adult kidney transplant setting. In this proposal, we will conduct a phase 1 trial of TRACT in 12 recipients of HLA mismatched living donor renal transplants. In order to reach our target number of subjects that are needed to complete the study, we plan to recruit and consent up to 20 subjects, as we anticipate either screen failure or withdrawal from the study is a possibility prior to initiation of study involvement. Initiation of study involvement is defined as the administration of the Treg cellular product (study drug). As Northwestern University has the largest living donor transplant program in North America (~ 160 patients per year) we are confident in our ability to recruit and enroll the patients required for this study in a timely manner.

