### **5.4 Early Withdrawal of Subjects**

#### ***5.4.1 When and How to Withdraw Subjects***

Patients have the right to withdraw from the study at any time for any reason. The investigator has a right to withdraw patients from the study in the event of intercurrent illness, adverse events, protocol violations, or other reasons, which will be explained to the subject(s) should this occur.

Subjects must be withdrawn from the study for the following reasons:

- The subject desires to discontinue participation in this study.
- The subject is unwilling or unable to comply with the protocol.
- Subjects who prematurely withdraw from the study prior to the administration of TRACT will be replaced at the respective TRACT dose level. The reasons for withdrawal must be recorded in the subject's file.
- Subjects who withdraw from the study subsequent to the administration of TRACT will still be evaluated for safety and survival as part of their standard of care and will not be replaced at the respective TRACT dose level. The reasons for withdrawal must be recorded in the subject's file.

Patient withdrawal from the study for medical reasons or in association with an adverse event of

any kind will be followed for the life of the study as a study patient. Patients who voluntarily withdraw from the study will be counseled by the Principal Investigator as to the likely medical consequences of study withdrawal and will be referred for additional counseling (Pastoral Care, Social Work, Bioethics, and Psychiatry) if this is deemed appropriate. Upon withdrawal patients will be transitioned to standard immunosuppressive therapy and referred to a qualified transplant physician for follow-up.

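### The two-of-three stopping rule in section 7.5 stops only enrollment, an undefined term, and does not require pending TRACT infusions to be held

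*Protocol*

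**What the plan says.** Section 7.5 sets out two collective rules. The first concerns acute toxicity: "The study as a whole will be halted if 2/5 patients develop grade 3-4 infusion reactions", or grade 4 organ toxicity in the first 30 days, and it also covers a death arising from those events. The second concerns two of three consecutive subjects with steroid-resistant or vascular rejection, loss of the graft, malignancy, serious infection or death. Its action is different: "in a period of 3 months, enrollment will be stopped and the study reassessed by the investigators", together with the IND sponsor and the IND medical monitor. It does not mention infusions.

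The protocol does not define enrollment. Section 1.9 defines the start of study involvement as the giving of the Treg product, but section 7.5 does not use that term.

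Section 4.1 places the infusion 60 days after transplant.

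**The concern.** The purpose of a stopping rule is to fix the action before the data arrive. Here the two rules stand in the same section and prescribe different actions, so a reader can fairly take the second to be the narrower one. If enrollment means a step before treatment, stopping it leaves untouched any subject who is already transplanted and waiting for day 60.

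What is at stake is whether such a subject receives a single infusion, which cannot be taken back, while the investigators are still assessing a cluster of the gravest outcomes that the protocol lists. The text should settle that, and it does not.

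**Working it through.** The plan gives no figure to reproduce here. The check compares the passages and then does simple counting.

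**1. Which way is enrollment used?**

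| Place | Use | Reading it favours |
|---|---|---|
| Study Summary | "ESTIMATED ENROLLMENT: 12", which equals the number to be treated; section 1.9 allows up to 20 to be consented | Covers infusion |
| Section 7.4 | Enrollment into a dose level opens once the previous cohort has cleared its toxicity window | Can cover infusion |
| Section 4.1, text after the schedule of events | "The clinical site for recruitment, enrollment, and treatment of patients will be Northwestern Memorial Hospital" | A step separate from treatment |
| Section 7.6.1 | Baseline status is described as at enrollment | A step before treatment |

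Under the first reading the rule stops infusions. Under the second it does not. The text does not choose between them.

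**2. Can a subject have passed enrollment and not yet been infused?**

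Inputs: leukapheresis 7 to 365 days before transplant (sections 2.2 and 6.2); infusion 60 days after transplant (section 4.1).

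- Transplant to infusion: 60 days.
- Leukapheresis to infusion: at least 7 + 60 = 67 days, at most 365 + 60 = 425 days.

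So under any pre-treatment reading there is a waiting period of about two months or more.

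**3. Does another provision require a hold on this trigger?**

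- *Review before the next patient and the next cohort (section 7.4).* It looks at toxicity reports and ends in a recommendation. The associated waiting period is 21 days and turns on dose-limiting toxicity. That definition leaves out events attributed to the transplant, intercurrent illness or other medication, and infections tied to neutropenia. Rejection, graft loss or severe infection may therefore not count.
- *Escalation gate (section 4.1).* The next dose is "administered to the next cohort of patients if there are no observed serious adverse events within 30 days of TRACT infusion". This is firm, but it governs the step to the next cohort and looks back 30 days. The section 7.5 trigger spans 3 months. The 3-month protocol biopsy, taking 3 months as 90 days, falls 90 − 60 = 30 days after infusion, so rejection found there may surface as the gate closes or later.
- *Weekly review, review before escalation, and termination by the principal investigator (sections 8.1, 9.4 and 7.5).* Each could stop an infusion. Each is discretionary.
- *Full halt (section 7.5).* It applies to some of the same cases, namely grade 4 organ toxicity within 30 days and deaths from the acute events, but not to the whole list.

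None of these mandates a hold when the two-of-three trigger fires.

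**4. How many further infusions at the same dose?**

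- Tier of 3, with at least 2 infused: at most 3 − 2 = 1 left, so 0 to 1.
- Tier expanded to 6, where expansion begins only after 3 are treated: at most 6 − 3 = 3 left, so 0 to 3.

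The first count takes both affected subjects to be in the same tier. If they fall in adjacent tiers, with one infused in the upper tier, 3 − 1 = 2 remain there. The second count takes exactly 3 subjects to be added, although section 7.4 sets 3 as a minimum. Neither count includes infusions planned at the next dose after the escalation gate has cleared. The protocol does not say how many subjects will be transplanted and waiting at any moment.

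**The case against.** The strongest reply is that no infusion goes ahead by default. Under section 7.4 adverse event information decides whether the next subject is dosed, and dosing is to be adjusted for adverse events generally, which is wider than dose-limiting toxicity. The group that makes this review is largely the group to which section 7.5 gives the reassessment. For an infusion to slip through, those people would have to clear a patient while reassessing the study for graft loss or death. The nearest use of the contested word, in section 7.4, also ties enrollment to entry at a dose level, which closes the gap if it carries over. A graded response is defensible in itself: the second trigger has no relatedness test, infection and malignancy are known risks of the background immunosuppression, and an automatic hold can waste a fresh product.

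Much of this stands. It makes an infusion during the reassessment unlikely and keeps the point modest. It does not remove it. The dose-level usage is one of several, and the per-patient review rests on judgement or on a 21-day window, where the trigger covers 3 months. A graded response is a fair choice, but its lower grade should still say what happens to subjects awaiting infusion.

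**Conclusion.** The point holds as a gap in the wording of a safety rule. On the two-of-three trigger the protocol stops enrollment, does not define the word, and does not require pending infusions to be held. Severity is minor to moderate. The exposure is 0 to 1 further infusions at the same dose in a three-subject tier and 0 to 3 in an expanded tier, on the assumptions stated with those counts. The number of subjects waiting when the trigger fires is unknown and may be zero.

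Two stronger readings are not supported:

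- A reader might infer that the protocol lets infusions continue freely during the reassessment. It does not: section 7.4 puts a review before each next patient and each next cohort.
- A reader might use the calendar ("ESTIMATED STUDY COMPLETION: MARCH 2016", the other estimated dates, or the 21-day spacing) to work out how many subjects would be waiting or infused. The dates are estimates. An average over the whole accrual period includes time when the trigger cannot yet fire, and the spacing alone ignores the reviews and the cohort gate. Neither measures exposure at the trigger.

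**What to change.** In section 7.5, replace the words that stop enrollment with: *enrollment and all further TRACT infusions will be suspended until the reassessment is documented*. Add that subjects who miss their infusion through the hold are treated as withdrawals before TRACT. Section 5.4.1 already provides for them: "Subjects who prematurely withdraw from the study prior to the administration of TRACT will be replaced at the respective TRACT dose level". This applies if the study resumes.

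The edit is one phrase and a cross-reference. If the sponsor already intends a hold, only the clarity changes.

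The real cost is product. The final cells are given fresh and never frozen, and they come from a single leukapheresis course. Manufacture starts about 21 days before infusion, near day 60 − 21 = 39 after transplant, so a hold that falls between then and day 60 may lose a culture under way. Replacements would draw on the margin between the 20 subjects who may be consented and the 12 to be treated: 20 − 12 = 8, which also has to cover screen failures and other early withdrawals.
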